### Data collection

Wearable data and ePRO data will be transmitted by monti via mobile data services to a centralized server that runs real-time data analysis and analysis software. The data recorded by the wearable will include time-series data of raw signals as well as vital signs and physical activity parameters, with the latter computed using proprietary algorithms provided by the manufacturer. Vital signs and physical activity parameters, such as heart rate, temperature, respiratory rate, and physical activity, will be recorded at a rate of up to 1 Hz. Thus, up to 3600 data points are potentially generated per hour, each paired by a corresponding quality index. On the platform backend, data integrity is assessed by monitoring actual wearing time, both initial and ongoing app usage, and overall data quality. Data integrity assessments are conducted at interim study visits and the study’s conclusion (*Table 2*).

Clinical records (visit entries, laboratory results, diagnostic results) will be documented in worksheets. Records will be independently and retrospectively reviewed by two cardiologists for the presence of ADHF. Worksheet entries and results of the validated questionnaires are transferred into a database.

Time-series data recorded by the wearable will be annotated based on clinical records. At each follow-up visit, where a clinical congestion assessment is conducted, the 2 days prior and post-visit are annotated as either ADHF or regular, as determined by the congestion assessment on the visit day.

Exploratively, the dataset of regular episodes may be enriched by including episodes beyond this initial 2-day window if patients report stable symptoms and vital signs through the app. This approach allows for the evaluation of whether these additional episodes show consistent ‘regular’ patterns suitable for model training. Datasets will be split into hours according to their timestamps, and only hours with a >90% amount of data points will be included to ensure sufficient information content among hours. No predefined quality constraints are used.

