To calculate the risk index, ‘regular’ hours collected during the study are used to train a deep neural network with a self-supervised contrastive learning objective, extracting features typical of regular periods. Training and test data are split 90/10. The model is used to calculate a risk index that measures the dissimilarity to regular features. The detection and predictive performance of the risk index will be compared to clinical documentation of ADHF. To evaluate the risk index’s predictive capabilities over time, the timestamp of the clinical ADHF diagnosis will be used as a reference point. The risk index computed by the model will subsequently be examined for the days preceding an ADHF event. This analysis aims to identify early deviations in the risk index that could potentially be driven by subclinical changes in physical activity or vital sign patterns.

Data collection will be conducted following an intention-to-treat approach and will continue until withdrawal, except in cases where there is a specific request to delete all individually recorded data.

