### Outcome and objectives

The primary outcome of this pilot study with the monti platform will be the accuracy of detecting episodes with diagnosed ADHF by a self-supervised contrastive learning-derived risk index based on wearable-recorded time series assessed through *C*-statistics (*Table 4*). As a secondary outcome data integrity will be assessed through the percentage of wearable data per day, the time difference between logged time point of measurement and database, and the score in the SUS, will be evaluated. Additionally, several exploratory endpoints will be examined.

**Table 4 ztaf004-T4:** Objectives and outcome measures of the CONAN study

	Outcome measures
Primary objective	
Assess the capability of the self-supervised contrastive learning-derived risk index (from wearable-recorded time series) to detect episodes of acute decompensated heart failure (ADHF).	Area under the receiver operating characteristics (AUROC) curve for detecting episodes of diagnosed ADHF.
Secondary objective	
(2) Evaluate the data integrity of the *monti*-monitoring platform in terms of adherence, technical functionality, and data quality.	Adherence: Daily percentage of wearable data availability. Percentage of data availability over participation period. Availability of each parameter per day. Number of app-server connection attempts. Number of uploaded vital signs. Number of recorded ECGs. Number of dropouts. Technical functionality: Ratio of failed uploads to total uploads. Number/type of notifications sent via the app. Number/type of user contacts. Mean time difference between measurement and database logging. Data quality: Mean percentage of data with high quality indices determined by the wearable for each parameter per day.
(3) To assess usability of the mobile *monti* platform	Mean score on the System Usability Scale (SUS). Percentage of users rating the app as ‘easy to use.’
(4) Monitor adverse events, including device-related effects and deficiencies.	Number of skin reactions or discomfort. Number of observed device damages.
Explorative objective	
(5) Expansion of the dataset by including additional ‘regular’ episodes	Number of ‘regular’ episodes included for training, annotated based on the 2-day window of study visits. Number of the additional ‘regular’ episodes included for training, annotated based on patient-reported stable symptoms and vital signs via the app. AUROC detecting episodes with diagnosed ADHF with expanded training data.

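### Hours enter training and testing on completeness alone, so poor-quality hours can distort the primary AUROC in either direction, and the plan as written cannot separate this from ADHF detection

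*Protocol article*

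**What the plan says.** The Data collection section of the protocol article splits the wearable data into hours and sets one entry condition: "only hours with a >90% amount of data points will be included to ensure sufficient information content among hours". The next sentence reads: "No predefined quality constraints are used".

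The same section shows that the information for a quality condition exists. For vital signs and activity, "up to 3600 data points are potentially generated per hour, each paired by a corresponding quality index". As part of its integrity checks, the backend also tracks how long the device is actually worn and how good the recordings are.

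Both sources serve the data-integrity objective. In Table 4 (Outcome and objectives) the quality index appears only as a descriptive secondary measure: "Mean percentage of data with high quality indices determined by the wearable for each parameter per day". Nothing in the article uses the quality index or wearing time to select hours, or to repeat the primary analysis.

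The hours labelled regular train the network ("Training and test data are split 90/10"). The resulting index expresses how far observed features lie from those of regular periods, and its AUROC for ADHF episodes is the primary outcome. The Limitations section makes the reliability of the index depend on both the amount and the quality of the training data.

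**The concern.** The completeness rule is meant to secure information content, but counting values does not do so. Heart rate, respiration and similar parameters come from the manufacturer's algorithms. An hour with a loose band can return a full set of values and still be unreliable.

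An index built on distance from normal has no stated means of telling artefact from congestion:

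- In a test hour, artefact can score as abnormal.
- In a regular training hour, artefact can be learned as part of normal.

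ADHF and regular labels attach to windows around different kinds of visit (discharge, routine outpatient, unplanned or emergency). It is plausible, though the article does not show it, that wear and signal quality differ between them.

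If they differ, part of the AUROC measures device handling. If they do not, artefact can weaken real detection. What is at stake is how the primary result may be read: the planned analysis yields one AUROC, with nothing prespecified to show which explanation applies.

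**Working it through.** **Figure to reproduce.** The plan gives none on this point. Its sample size of about 282 (Statistical analysis) does not depend on which hours are admitted.

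**Inputs from the article.** Entry on more than 90% of points; no predefined quality constraint; quality index per point recorded; wearing time monitored; primary measure AUROC.

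**Assumed inputs.** The article gives no artefact shares. Let pA and pR be the shares of low-quality hours in ADHF and regular windows, and A the AUROC among clean hours. As a worst case, let every low-quality hour outrank every clean hour, with ties between low-quality hours split evenly.

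**Formula.** Draw one ADHF hour and one regular hour:

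- both clean, probability (1 − pA)(1 − pR): the ADHF hour ranks higher with probability A
- only the ADHF hour low-quality, probability pA(1 − pR): it always ranks higher
- only the regular hour low-quality, probability (1 − pA)pR: the ADHF hour never ranks higher
- both low-quality, probability pA·pR: 0.5

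Observed AUROC = (1 − pA)(1 − pR)·A + pA(1 − pR) + 0.5·pA·pR. With no signal (A = 0.5) this reduces to 0.5 + 0.5(pA − pR).

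**Results.**

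| A | pA | pR | Calculation | Observed AUROC |
|---|---|---|---|---|
| 0.50 | 25% | 10% | 0.5 + 0.5 × 0.15 | 0.575 |
| 0.50 | 10% | 25% | 0.5 − 0.5 × 0.15 | 0.425 |
| 0.85 | 20% | 20% | 0.544 + 0.16 + 0.02 | 0.724 |
| 0.80 | 20% | 20% | 0.512 + 0.16 + 0.02 | 0.692 |
| 0.80 | 5% | 20% | 0.608 + 0.04 + 0.005 | 0.653 |
| 0.80 | 20% | 5% | 0.608 + 0.19 + 0.005 | 0.803 |

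The first two rows show that the sign follows the imbalance. The last row shows that dilution and imbalance can nearly cancel, so an unremarkable AUROC does not rule out either.

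**A milder case.** Suppose artefact has been learned as regular, so that low-quality hours score like clean regular hours. The observed AUROC is then (1 − pA)·A + 0.5·pA. For A = 0.85 and pA = 20% this is 0.68 + 0.10 = 0.78 instead of 0.724. For A = 0.5 it stays at 0.5.

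**Hours and episodes.** The calculation is per hour, while Table 4 defines the outcome per episode. The article does not say how hours combine into an episode score. If they are averaged, scattered poor hours matter less than shown; poor wear lasting a whole window would not average out.

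**The case against.** The strongest case on the other side has five parts.

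- **The rule is a stated choice in a pilot.** Unfiltered hours reflect real use, and the Discussion wants the model to cover rest and activity, inpatient and outpatient settings. If quality flags fall with movement (an assumption), a hard filter would remove active hours selectively. This stands, and it is why the primary rule should not simply be replaced.
- **The worst case is in tension with the training step.** If a fifth of the training hours are artefact, such hours need not be the most dissimilar. This also stands: the tabulated figures are worst cases, and the milder case is smaller.
- **The completeness rule may already remove unworn hours.** It would if the device stops logging off the wrist. The article does not say. A reader might infer that unworn hours enter the model, but the text does not support that. Badly worn hours that still return values remain possible.
- **Quality is not ignored.** It is reported per parameter and day, and platform deficiencies are to be analysed. Neither is linked to the AUROC, so neither shows whether the primary result depends on it.
- **A sensitivity analysis is detail for an analysis plan.** That would answer a complaint about a missing analysis alone. Here the article fixes the admission rule and expressly sets quality constraints aside, while its own Limitations section makes the index depend on training-data quality.

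Low quality may also be a genuine consequence of decompensation. That does not remove the ambiguity; it is a reason to measure how well quality alone separates the labels.

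**Conclusion.** The concern holds as a statement about what the primary AUROC can be taken to show. Selection on completeness alone lets poor-quality hours into both training and testing, and the plan as written does not separate their effect from ADHF detection.

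A reader might go further and infer that the AUROC will be inflated. The documents do not support that: they give no artefact shares and no distribution of the quality index by label, and the effect can go either way. The range from 0.425 to 0.575 without any signal, and the fall from 0.85 to 0.724 with equal 20% shares, rest on assumed shares, on artefact hours outranking all others, and on scoring by hour. Nor does the text show that the rule is indefensible as a primary choice. The weakness can be remedied cheaply, and the remedy changes what the trial can conclude.

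**What to change.** Keep the current admission rule for the primary analysis and prespecify three additions:

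- **(a)** The primary AUROC repeated on worn, high-quality hours, with the quality and wear threshold fixed before the index is examined and applied without knowledge of the ADHF or regular label.
- **(b)** The AUROC of the quality index and wear measure alone, as a negative control. Count separation in either direction, since 0.425 is as informative here as 0.575.
- **(c)** The distribution of quality and wear by label.

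State in advance that detection will be attributed to ADHF physiology only if the result holds in (a), by a criterion also written down beforehand, and the primary AUROC exceeds (b) with a confidence interval for the difference lying above zero. That interval should allow for repeated hours from the same patient.

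The cost is two extra runs and one descriptive table on data already recorded, with no new patients or procedures. The downside is that (a) will rest on fewer hours, possibly with less physical activity among them. This is a reason to report (a) beside the primary result and not in its place.

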### Statistical analysis

The sample size calculation was based on a 20% incidence rate of congestion, an 85% detection sensitivity of the risk index (see below), a 15% dropout rate, a 10% error tolerance, and a significance level of 0.05, indicating a need for ∼282 patients to achieve sufficient statistical power.

For statistical analysis differences between means of hours annotated as ‘regular’ and ‘congested’ obtained from risk score will be tested for significance using a two-sided *t*-test test, adjustment for multiple comparisons is performed by using Bonferroni correction. To address overfitting, a 10-fold cross-validation will be performed. Statistical significance will be tested by an analysis of variance within the cross-validation splits of ADHF and regular. Receiver operating characteristics analysis [area under the curve of the ROC-analysis (AUROC)] will be computed to assess the primary endpoint. The cut-point that optimizes the detection of true positive results (sensitivity) and false positive results (1-specificity) is reported by the Youden index. For clinical requirements (not missing an event), specificity will additionally be reported at a sensitivity of ∼95%.

To assess risk score prediction capabilities for congestion detection, the performance of the score up to 7 days before and after the timestamp of diagnosis (t = 0 h) will be analysed. For AUROC-analysis, 95% confidence intervals are reported. A *P*-value of <0.05 will be considered significant. For data and statistical analysis, an open-source software tool will be used.

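### The 90/10 split and the 10-fold cross-validation name no grouping unit; if single hours are allocated, the primary AUROC can be biased in favour of the index

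*Protocol article*

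**What the plan says.** All references are to the protocol article.

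- **Unit of model data** (Methods, Data collection): "Datasets will be split into hours according to their timestamps, and only hours with a >90% amount of data points will be included".
- **Labels** (Data collection): at each follow-up visit with a congestion assessment, "the 2 days prior and post-visit are annotated as either ADHF or regular, as determined by the congestion assessment on the visit day". One assessment therefore labels about four days of one patient.
- **Training material** (Data collection): the regular "hours collected during the study are used to train a deep neural network with a self-supervised contrastive learning objective". ADHF hours are not training material. The risk index measures how far an observation lies from the features learned from regular periods.
- **Split** (Data collection, directly after the training sentence): "Training and test data are split 90/10".
- **Cross-validation** (Statistical analysis): "To address overfitting, a 10-fold cross-validation will be performed".
- **Test of means** (Statistical analysis): it compares "differences between means of hours annotated as" regular and congested, so the hour is the unit there too.
- **Primary outcome** (Outcome and objectives, Table 4): the AUROC for detecting ADHF episodes. The Youden cut-point and the specificity at a sensitivity of about 95% are reported alongside it.

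The article nowhere mentions grouping the split or the folds by patient or by visit window.

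**The concern.** The model learns from one class only, and its score is a distance from what it has learned. Two things can then raise the score: a real physiological change in ADHF, or the hour coming from a stretch of recording that the model has not seen. A valid evaluation must make the second equal for both classes.

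An hour-level split does not. A held-out regular hour comes from a patient and a four-day window that are largely in training. An ADHF hour never has hours of its own window in training, because no ADHF window is trained on. Familiarity then goes with the class label, in the direction of the study hypothesis. Every fold of a cross-validation over hours repeats the imbalance, so the stated safeguard against overfitting would not work against this form of it.

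At stake are the primary AUROC and the two operating points. Regular hours that score too low also pull the cut-point down, so a new patient's regular hours would raise more false alarms than the study reports. The exploratory AUROCs in Table 4 would be affected in the same way.

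**Working it through.** **1. The plan's own figure.** The sample size follows from the precision of sensitivity: 1.96² × 0.85 × 0.15 / 0.10² = 48.98 ADHF cases; 48.98 / 0.20 = 244.9; 244.9 × 1.15 = 281.6, which is the stated 282. Nothing in it depends on how data are split, so it does not change. The article gives no target AUROC to reproduce.

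**2. Which unit is meant?** The sentence on the 90/10 split follows the sentence that trains on regular hours. The recordings are cut into hours, and the test of means is on hours. Episodes appear only as the target of the AUROC, not as the unit of allocation. The text points to hours but does not say so.

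**3. How uneven would familiarity be?** A window of 2 days before and 2 days after a visit has at most about 4 × 24 = 96 hours. With H usable hours per window and 90% of hours in training, a regular test hour has on average 0.9 × (H − 1) hours of its own window in training:

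| Usable hours H | Regular test hour | ADHF hour |
|---|---|---|
| 96 | 0.9 × 95 = 85.5 | 0 |
| 24 | 0.9 × 23 = 20.7 | 0 |
| 4 | 0.9 × 3 = 2.7 | 0 |

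Ten folds also train on 90% each time, so the counts are the same.

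**4. What could this do to the AUROC?** The article gives no correlations, so this step rests on assumptions:

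- Each of 8 features is the sum of independent normal patient, window and hour terms with standard deviations σp, σw and σe.
- Each patient has two regular windows, and 20% of patients have one ADHF window as well. Each window has 40 usable hours.
- The index is the mean distance to the 5 nearest training hours, with 10 folds.
- There is **no ADHF effect**, so a fair evaluation should give about 0.5.

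The share of variance between patients and windows is (σp² + σw²) / (σp² + σw² + σe²). For example, (1 + 0.49) / (1 + 0.49 + 0.16) = 0.90.

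| σp, σw, σe | Share | Split by hour | By window | By patient |
|---|---|---|---|---|
| 1, 0.3, 1.5 | 0.33 | 0.490 | 0.488 | 0.491 |
| 1, 0.7, 1.5 | 0.40 | 0.493 | 0.489 | 0.491 |
| 1, 0.3, 0.7 | 0.69 | 0.507 | 0.462 | 0.489 |
| 1, 0.7, 0.7 | 0.75 | 0.574 | 0.478 | 0.487 |
| 1, 1, 0.7 | 0.80 | 0.710 | 0.466 | 0.477 |
| 1, 0.7, 0.4 | 0.90 | 0.934 | 0.452 | 0.479 |
| 1, 1, 0.4 | 0.93 | 0.975 | 0.460 | 0.482 |

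The first four rows use 245 patients and 6 runs, the last three 120 patients and 12 runs. The simulation standard error is at most about 0.02 throughout.

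A separate null simulation varied the number of features, with a patient share of 0.3 to 0.4 and window shares of 0.2 / 0.3 / 0.4. Hour-level folds gave 0.51 / 0.52 / 0.64 with 8 features and 0.54 / 0.64 / 0.96 with 16. Patient-level folds stayed at 0.49 to 0.52.

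**The case against.** The strongest reply is that the article never states an hour-level split. Cutting a recording into hours is segmentation and is compatible with folds made of patients. Table 4 defines the primary outcome on episodes. A journal article condenses a fuller protocol, and the grouping of folds may be fixed there. This stands in part: a reader might infer that the folds are drawn over hours and that the AUROC is inflated, and the article supports neither as a statement of fact. It does not dispose of the point. The article fixes the proportion, the number of folds and their purpose, and the scheme as described is most naturally carried out over hours. Scoring by episode does not help either, because averaging over a window averages hours that all carry the same advantage.

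The second reply concerns size. At shares of 0.33 to 0.40 there is no inflation, and at 0.69 it is hardly visible. The nearest-neighbour rule rewards stored neighbours, whereas the trial's index comes from a learned representation whose tendency to memorise windows is unknown. It is also tempting to call the hours of a window near-duplicates. The Discussion supports only an unchanged congestion state within a window, and it expects patterns to vary between rest and activity. All of this stands, and it means that no size can be claimed.

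The third reply is that holding out whole windows also removes the upward bias (0.45 to 0.49 in the table), and that the Discussion wants the index to allow for individual variation. That is fair. It argues for a window-based analysis beside the patient-based one, not for allocating single hours.

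**Conclusion.** The point holds in conditional form. The held-out unit is not fixed, and the wording points to hours. If hours are allocated, regular test hours share patient and window with training hours, and ADHF hours have no same-window hours there. The primary AUROC, the Youden cut-point and the specificity at about 95% sensitivity can then be biased in favour of the index, and cross-validation over hours does not correct it.

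The imbalance itself follows from the design: 85.5 against 0 same-window training hours for a full window. Its effect on the AUROC cannot be fixed from the article. With no true effect, the simulated values run from 0.49 to 0.98, depending on the assumed variance shares, number of features and distance rule. Where the distortion was material it was upward. The results show that an impressive AUROC could arise without any ADHF signal; they do not show that this trial's AUROC will be inflated.

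**What to change.** State that the 90/10 split and the ten folds are made of whole patients: all regular and ADHF hours of a patient are held out together and scored by a model that never saw that patient. Take the AUROC, the Youden cut-point and the specificity at about 95% sensitivity from those held-out scores.

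If a personalised index that uses the patient's own history is intended, name it as an additional analysis that holds out whole visit windows in time order. Do not allocate single hours to folds in either analysis. If the full protocol already groups by patient, one sentence confirming this is enough.

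The cost is a sentence in the plan and slightly more coding for grouped folds. The reported AUROC may be lower. The number of patients does not change. The choice should be made before results are seen.
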